**Figure 1 F1:**
[figure not shown]
**Planned baseline CONSORT 2010 flow diagram for cancer detection analysis.** All batches of women attending routine digital mammography screening at participating centres during the trial will be randomised to either the intervention or control group. Follow-up data may not be available for a small proportion of women who either do not attend a recall for assessment or for whom records are not updated at the point of data collection. NBSS, National Breast Screening Service.

### Recruitment

There are 80 breast screening centres in England. About 44 breast screening centres will be recruited into the trial (depending on centre size), which will last for 1 year, 4 months. After the first year of the trial (allowing 2 months for follow-up appointments to determine which women have cancer), the data for 1 year of screening at 44 centres will be downloaded and analysis of the primary outcome of cancer detection rate and the secondary outcomes will be completed. Analysis of missed cancer rates will be undertaken at 3 years after completion of the administration of the intervention.

There will be no extra time commitment for NHS staff in administering the trial at each centre, as the design is fully computerised and changes to batch reading orders will be automatically downloaded using each centre’s latest software update. Importantly, this scheme is anticipated to help with reaching recruitment targets.

### Eligibility

To be included, screening centres must use double-reading of screening mammograms and must have at least one piece of digital mammography equipment used for screening. All women who undergo mammography screening using digital equipment during the study period at the study centres will be included.

Centres which use single reading of mammograms, centres that have no digital mammography equipment used for screening (for example, the software intervention does not work in the old equipment) and women who attend symptomatic breast clinics will be excluded.

### Postrandomisation withdrawals and exclusions

Centres participating may withdraw from the trial at any time without prejudice. Upon withdrawal, or at any time before the data is analysed, centres can choose whether their data is collected and used in the analysis. Initial survey results describing centre characteristics will be used to analyse patterns of withdrawals from the trial, unless the centre requests that their data not be used in this way.

### Compliance and contamination

Compliance is expected to be very high because, after centre-level consent is given, all implementation is automated. In addition, deviation from the protocol would be very difficult. There is no method available to move cases between intervention and control groups. Case order can be changed manually by selecting the ‘ignore’ option rather than inputting a screening result, so that either the mammogram can be reviewed at a later stage or a result can be input and revised later. These events will change the reading order and produce some level of contamination. However, analysis will be based on intended order of reading. Data will also be collected on actual reading order to measure levels of contamination and their effects on outcomes. These effects are expected to be extremely small (on the order of 1 per 500 cases) because screening is a fast-moving, high-volume activity, and there is little time in practice to change reading order or to come back to cases at a later stage. Full data management procedures can be found in the statistical analysis plan.

### Consent

Informed consent will be obtained at the centre level from the director of the service, who is also usually the lead reader. Consent will be obtained at the centre level rather than by patient or reader because it is at this level that the intervention is applied. In addition, the intervention can be considered an alternative form of standard practice because no aspect of the way in which the mammograms are reviewed or evaluated is altered other than the reading order.

Directors of breast screening centres will be contacted in the first instance by email introducing the study with a copy of the participant information sheet and informed consent form attached. They will then receive a follow-up telephone call 1 week later. Each centre director will be offered a copy of the research protocol and the Integrated Research Application System ethics form and a visit from one member of the investigation team to introduce the study if desired. The study software embedded in the NBSS software will remain inactive until a signed consent form is received from the centre and local research and development approvals are granted, at which point it can be activated simply and quickly. The study can commence in each centre by simply changing the software settings to activate the intervention.

In the unlikely event that information becomes available which may be relevant to the participant’s willingness to continue participating in the trial (for example, findings from other research studies), then the directors of every participating breast screening centre will be informed immediately by email and follow-up telephone call.

### Recruitment and randomisation

The rate of accrual will be monitored at the centre level. If it falls appreciably below the projected level, the reasons will be identified and remedial actions will be taken to protect the power of the trial and alleviate concerns about selective entry and other aspects of quality. Randomisation will be automatically computer-generated at the point at which the batch is ready to be read on the NBSS system. Only batches of cases to be read as part of the NHS breast screening programme will be randomised. Cases from symptomatic clinics will be excluded prior to randomisation. Randomisation will be carried out with equal probability to one of four groups: control (both read in appointment order: ↓↓), control (both read in reverse appointment order: ↑↑), intervention (first reader in appointment order and second reader in reverse appointment order: ↓↑) and intervention (first reader in reverse appointment order and second reader in appointment order ↑↓).

### Blinding

The women screened will not be aware of whether their mammograms are read as part of an intervention or a control batch. The readers will not know the arm of the trial to which each batch has been assigned, because batches will be read in appointment order and reverse appointment order in both arms of the trial.

## Discussion

The experimental design is between subjects, so readers will not be burdened with reading cases twice (once in each experimental condition). This design has lower statistical power than a within-participant approach, however, so recruitment targets are high to achieve 80% power. Sensitivity analysis for the estimate of effect size indicates that it is very sensitive to small changes in effect size. If the effect size is as low as 200 extra cancers detected per year in England, it may still be considered clinically significant, but overall sample size would need to be 14 million women to detect such an effect. Achieving a sample of this size would be unrealistic; therefore, there is a risk of the trial being underpowered. However, an effect size of 200 extra cancers detected in England each year would be detectable in the form of a surrogate for cancer detection rate, which is the rate of disagreements between readers. This parameter is included as a secondary outcome. If recruitment targets are not met, then the rate of disagreements, as a surrogate for cancer detection rate, may have to be used as the primary outcome.

One possible mechanism for harm from the intervention is associated with reading the cases in reverse appointment order, which is not currently standard practice. To blind the readers to group allocation, however, reading in reverse appointment order is present equally in the intervention and control groups, so a two-tailed test would not detect this harm. Therefore, a secondary analysis of recall rate and cancer detection rate of cases read in appointment order and reverse appointment order will be carried out to determine whether reading a batch in reverse appointment order affects performance.

This study is a pragmatic multicentre, two-arm, double-blind, cluster randomised controlled trial of a computer software intervention designed to reduce the effects of a vigilance decrement in breast cancer screening. The intervention and randomisation are applied automatically using computer software, thus reducing the cost of running the trial and limiting the possibility of allocation and treatment bias. This study design also reduces the administrative burden on participating centres, thus removing one of the barriers to participation. The trial is double-blinded because neither the women screened nor the readers will be aware of whether each batch is in the intervention or control group.

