**Methods/Design:**

The CO-OPS study is a pragmatic, multi-centre, two-arm, double blind cluster randomised controlled trial of a computer software intervention designed to reduce the effects of a vigilance decrement in breast cancer screening. The unit of randomisation is the batch. Intervention batches will be examined in the opposite order by the two readers (one forwards, one backwards). Control batches will be read in the same order as one another, as is current standard practice. The hypothesis is that cancer detection rates will be higher in the intervention group because each readers’ peak performance will occur when examining different women’s mammograms. The trial will take place in 44 English breast screening centres for 1 year and 4 months. The primary outcome is cancer detection rate, which will be extracted from computer records after 1 year of the trial. The secondary outcomes include rate of disagreement between readers (a more statistically powerful surrogate for cancer detection rate), recall rate, positive predictive value, and interval cancer rate (cancers found between screening rounds which will be measured three years after the end of the trial).

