### Trial aims and outcomes

The primary aim of the trial is to determine whether presenting the cases to the first and second readers in the order opposite one another increases the cancer detection rate (true-positive rate). The secondary aims and outcome measures of the trial are as follows:

1. Is there a difference in the number of disagreements between readers in each study arm? This is the proposed mechanism by which an increase in cancer detection rate occurs and therefore acts as a surrogate outcome, particularly if the effect size is smaller than anticipated or recruitment targets are not met. The rate of disagreement refers to the proportion of cases for which one reader thought the case should be recalled and the other reader thought the case should not be recalled.

2. Is there a difference in 3-year interval cancer rate in each study arm? Furthermore, as the interval cancer rate can be considered an approximation of the false-negative rate, is this change (if any) concurrent with changes in the cancer detection rate between study arms (primary outcome)? The interval cancer rate is measured as the rate of cancers detected symptomatically in the 3 years subsequent to screening and therefore will be collected 3 years after the trial implementation is complete.

3. Do the recall rate and positive predictive value (PPV) differ between the study arms?

4. With regard to NHS considerations, is the intervention cost-effective when compared with the control arm? The lifetime cost-effectiveness of the intervention will be modelled using the primary outcome from the trial. Are there any effects introduced by the trial methodology? Specifically, are the cancer detection and recall rates affected by introducing reverse reading order? The cancer detection rate and the recall rate for both versions of the control arm (↓↓ and ↑↑) will be compared to measure any adverse effects of reading in reverse order.

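### The Discussion leaves open a switch of the primary outcome to reader disagreement, an endpoint that counts women with and without cancer alike and cannot by itself show that more cancers are found

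*Protocol article*

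**What the plan says.** The Abstract (Methods/Design) states without condition: "The primary outcome is cancer detection rate". It lists disagreement between readers as a secondary outcome and calls it "a more statistically powerful surrogate for cancer detection rate".

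Trial aims and outcomes, item 1, presents disagreement as the proposed mechanism and says that it "acts as a surrogate outcome, particularly if the effect size is smaller than anticipated or recruitment targets are not met". It defines a disagreement as a case where "one reader thought the case should be recalled and the other reader thought the case should not be recalled". Cancer status plays no part in that definition.

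The Discussion concedes that the trial cannot detect a small effect on cancer detection, then asserts that "an effect size of 200 extra cancers detected in England each year would be detectable in the form of a surrogate". Its next step is the switch: under a recruitment shortfall, "the rate of disagreements, as a surrogate for cancer detection rate, may have to be used as the primary outcome". The article does not say how large a shortfall counts, when the decision would be taken, or by whom.

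Secondary analyses feeds the trial's primary outcome into the lifetime cost-effectiveness model, to represent a change in the cancer detection rate.

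**The concern.** A primary outcome decides what a trial may conclude. Here the question could change from whether more cancers are found to whether the two readers differ more often. The second does not answer the first. If readers' threshold for recalling healthy women drifts along a batch, opposite reading orders will raise disagreement without finding one more cancer. The visible consequences would be more arbitration and possibly more false-positive recalls.

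The two places raise different problems. The Discussion allows the primary label to move, on a trigger that is undefined. Item 1 of the aims leaves disagreement secondary, but lets its weight grow when the effect is smaller than hoped. That can be known only after looking at the cancer result, so the added weight would be data-driven.

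A switch would also break the article's own economic plan, because a disagreement rate cannot serve as the detection-rate input that the model needs.

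**Working it through.** **1. The plan's own sample size.** Inputs from Power and sample size: 7.8 against 8.3 cancers per 1,000, two-sided 5%, 80% power. The standard two-proportion formula gives 501,398 per arm; the article states 501,361, so it reproduces. The stated 546,890 after clustering implies a design effect of 546,890 / 501,361 = 1.0908, which matches the stated 1.09. (The rounded ICC gives 1 + 39 × 0.002 = 1.078, a gap of about 1.2% that fits rounding of the ICC.) The effective size per arm used below is therefore 501,361.

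**2. Does a shortfall force a switch?** Power of cancer detection rate for the planned +0.5 per 1,000 is 80% at full recruitment, 76% at 90%, 68% at 75% and 51% at 50%. Power is lost gradually.

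**3. The small effect.** 14,700 cancers a year at 7.8 per 1,000 implies 14,700 / 0.0078 = 1.885 million women, so 200 extra cancers is 200 / 1.885 million = 0.1061 per 1,000. With 82 centres × 25,000 = 2.05 million women, it is 0.0976 per 1,000. For 0.1061 per 1,000, cancer detection rate has only about 9% power even at full recruitment, so this is where disagreement would carry the argument.

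**4. What disagreement would have to show.** The article gives no disagreement rate, so I assume a baseline q of 2% to 8%. The smallest difference d detectable with 80% power solves

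501,361 = [1.96·√(2p̄(1−p̄)) + 0.84·√(q(1−q) + (q+d)(1−q−d))]² / d², where p̄ = q + d/2.

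| Assumed q | d per 1,000 | d / 0.1061 | d / 0.0976 |
|---|---|---|---|
| 2% | 0.791 | 7.5 | 8.1 |
| 3% | 0.962 | 9.1 | 9.9 |
| 5% | 1.227 | 11.6 | 12.6 |
| 8% | 1.525 | 14.4 | 15.6 |

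So about 7 to 16 extra disagreements must accompany each extra cancer. At half recruitment, the situation that would trigger the switch, the first ratio column runs from about 11 to 20.

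**5. How many of these can be in women with cancer?** Take a reader's sensitivity as a at one end of the batch and b at the other, with readings independent given position and arbitration perfect.

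- Disagreements among cancers: same order a(1−a) + b(1−b); opposite order a + b − 2ab; difference (a−b)².
- Detected by at least one reader: same order 1 − [(1−a)² + (1−b)²]/2; opposite order 1 − (1−a)(1−b); difference (a−b)²/2.

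That is two cancer disagreements per extra cancer. The share in women without cancer would then be 1 − 2/7.5 = 73% up to 1 − 2/15.6 = 87%.

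**6. Is that composition plausible?** Epidemiology and burden of breast cancer gives 40 recalls per 1,000, of which 32 are false positives. Women without cancer can readily supply most disagreements, and for that reason a significant rise need not reflect cancers.

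**The case against.** A reader might infer that the trial could claim success with no evidence on cancers at all. The document does not support that. Cancer detection, recall and positive predictive value are analysed regardless, and three-year interval cancers are collected to show whether fewer were missed. The supported statement is narrower: the primary result could be positive without a demonstrated increase in cancers.

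A reader might also read item 1 of the aims as a second switch of the primary outcome, giving two chances at 5%, or 1 − 0.95² = 9.75%. That does not apply. Item 1 does not change the primary outcome, no rule lets either test count as success, and the two outcomes are linked by design. The Discussion's only trigger is recruitment. Accrual is monitored by centre and the article says there will be no interim data, so the decision could be made without sight of arm results. Made that way, it does not inflate type I error.

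Disagreement is not worthless as a surrogate. In the model above it rises whenever detection rises, and the hypothesised mechanism covers all cases, so many non-cancer disagreements per extra cancer are compatible with it. The detectability claim is therefore unsupported here, not shown to be false, and a calculation may exist in the full protocol or analysis plan.

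Finally, 45 centres are already activated against about 44 needed, and the wording is conditional. The trigger may never be met, although centre size varies. This lowers the urgency, but the clause still permits a poorly defined switch.

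**Conclusion.** The point stands in limited form and should be fixed. The Discussion permits a discretionary change of primary outcome, with no stated threshold, timing or decision-maker, to an endpoint defined without regard to cancer. Item 1 of the aims adds weight to that endpoint on a condition visible only in the results. The objection is to the meaning of the endpoint and to data-driven interpretation, not to a quantified loss of error control.

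The size, about 7 to 16 extra disagreements per extra cancer with 73% to 87% of them in women without cancer, rests on three assumptions: a baseline disagreement rate of 2% to 8%; a design effect of 1.09 that was derived for cancer detection, the ICC for disagreement being unknown; and, for the percentages, independent readers with perfect arbitration. That the endpoint ignores cancer status depends on none of them.

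**What to change.** 1. In the Discussion, delete the sentence beginning "If recruitment targets are not met, then the rate of disagreements, as a surrogate for cancer detection rate, may have to be used as the". In item 1 of Trial aims and outcomes, where the text says disagreement "acts as a surrogate outcome, particularly if the effect size is smaller than anticipated or recruitment targets are not met", delete everything from the word after the comma.
2. State that cancer detection rate remains the sole primary outcome whatever recruitment is achieved, reported with its 95% confidence interval.
3. Keep disagreement as a secondary, mechanism outcome. Report it by final result (cancer, false-positive recall, arbitrated to no recall), with no claim of benefit resting on it alone. If the detectability sentence stays, say what rise in disagreement it assumes.
4. Optionally, if the 12-month numbers are short, allow a decision made blind to arm-level outcomes to extend the primary data window into the planned months 13 to 16.

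Items 1 to 3 are wording changes, and data collection had not begun when the article was written. Item 4 costs a later extraction and the follow-up allowance that goes with it. The real price is that a recruitment shortfall would have to be reported as a less precise primary result.

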### Trial status

The trial has National Health Service ethical approval, and the software has been activated in 45 centres in the United Kingdom. Data collection is due to start in February 2014.

### Trial steering committee

The fellowship advisory group also acts as the trial steering committee. There is no need for a data-monitoring committee, as there will be no interim data available to monitor.
